### Randomization and blinding

#### Sequence generation

Stratified randomization was conducted considering the location of each community health center.

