### Sample size

A previous study reported that 12.64% of patients with AF received appropriate anticoagulants in community health centers of Shanghai [34]. Intracluster correlation coefficient (ICC) was 0.02 [35], the power (1-β) was 90%, and the double-sided significance (α) was 0.05. In the pilot study, the proportion of appropriate anticoagulation increased to 28% in the intervention group, so we expected the proportion to be 28% in this study. Seven community health centers are in each group and we plan to enroll 30 patients from each community health center in the control group, meaning a sample size of 448, or 498 to allow for a 10% loss to follow-up.

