### Statistical analysis

Categorical data will be reported as frequencies and percentages (*n*, %), and a chi-square test will be used to detect any significant differences. Continuous data will be reported as mean ± SD (standard deviation) and compared using a *t*-test if it is on the Gaussian distribution. Otherwise, the data will be reported as the median (IQR (interquartile range)) and compared using the Mann-Whitney *U* test. Linear regression model will be used to compare the continuous data between the distinct groups, considering the interaction of time and allocation. Logistic regression model will be used to detect the effect of the interventions on the primary outcome. Kaplan-Meier (Log-rank test) and Cox proportional hazard models are to be used for the secondary outcomes and safety outcomes. To simplify the analysis, the follow-up time will be recorded as a unit of a month and regardless of start or end. The time will be calculated from this month, if it occurs in the former month; otherwise, it will be calculated from the next month. All outcomes will be evaluated with Mantel-Haenszel statistics and adjusted for the effect of clustering.

Per-protocol (PP) analysis and the intention-to-treat (ITT) analysis will be conducted after filling missing values by multiple imputations. The subgroup analyses will be conducted by whether the CDSS is installed and used in all general clinics or only the AF special consulting room. The sensitivity analyses will be performed by age strata, gender, resident district, and anticoagulants used.

All statistical analyses will be performed with IBM SPSS Statistics, version 26.0 (SPSS Inc) and R (version 4.0.5). A two-tailed *P* < 0.05 will be considered statistically significant.

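### Several analyses reach the primary outcome, none is named as decisive and the clustering adjustment is not specified, so with 7 centres per arm the 5% error rate is not assured

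*Protocol article*

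**What the plan says.** Allocation is by health centre. "Stratified randomization was conducted considering the location of each community health center", with eight centres in one district and six in the other, each split 1:1 (Implementation). The Sample size section allows for clustering: "Intracluster correlation coefficient (ICC) was 0.02".

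The Statistical analysis section then makes four statements that bear on between-arm comparisons:

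- Categorical data are compared by a chi-square test, and continuous data by a t-test or Mann-Whitney test.
- "Logistic regression model will be used to detect the effect of the interventions on the primary outcome". That sentence has no term for centre.
- "Linear regression model will be used to compare the continuous data between the distinct groups, considering the interaction of time and allocation". That sentence has no term for person or centre.
- "All outcomes will be evaluated with Mantel-Haenszel statistics and adjusted for the effect of clustering".

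Intention-to-treat and per-protocol analyses are both listed, unranked, and one two-sided 5% threshold applies throughout. District appears only as resident district, in the sensitivity analyses.

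**The concern.** Three of the named methods can be applied to the primary outcome, and two of them are written as tests on independent patients. The closing sentence promises a clustering adjustment but ties it to no method beyond Mantel-Haenszel statistics, for which no strata are given. With 14 centres, common ways of adjusting behave differently, and those that rely on a large number of clusters reject too often.

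The decision on the primary outcome could therefore depend on which of several P values is taken, and the data analysts are not blinded (Blinding).

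A smaller related point concerns PSQ-18, collected four times per patient, and the KAP questionnaire, completed three times per GP (Enrollment and follow-up). Ordinary linear regression, as named, does not recognise that repeated scores come from the same person.

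**Working it through.** **Inputs from the Sample size section.** Control: "12.64% of patients with AF received appropriate anticoagulants in community health centers of Shanghai". Intervention: "so we expected the proportion to be 28% in this study". ICC 0.02. "the power (1-β) was 90%, and the double-sided significance (α) was 0.05". Seven centres per arm, 30 patients per control centre, 448 in total, 498 after allowing for 10% loss.

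**Reproducing the plan's figure.** Control arm: 7 × 30 = 210. That leaves 448 − 210 = 238, or 34 per intervention centre.

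- Design effects: 1 + 29 × 0.02 = 1.58 (control) and 1 + 33 × 0.02 = 1.66 (intervention).
- Variance of the difference: 0.1264 × 0.8736 × 1.58/210 + 0.28 × 0.72 × 1.66/238 = 0.000831 + 0.001406 = 0.002237; SE = 0.0473.
- Standardised difference: (0.28 − 0.1264)/0.0473 = 3.248.
- Power with a normal reference: Φ(3.248 − 1.960) = 90.1%.
- 448/0.9 = 497.8, rounded up to 498.

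Both stated figures are reproduced. The sample size allows for the ICC but uses a normal reference, as if there were many clusters.

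**Unadjusted tests, analytically.** The mean centre size is 448/14 = 32, so the design effect is 1 + 31 × 0.02 = 1.62. A test that ignores it has true error 2[1 − Φ(1.96/√1.62)] = 2[1 − Φ(1.54)] = 12.4%.

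**Simulation with no true effect.** Beta-binomial data, 7 × 30 against 7 × 34 patients, districts of 4+4 and 3+3 centres, no district effect, 20,000 trials per setting. Common proportion 12.64%, 20% or 28%. ICC 0.02 is the article's; 0.05 and 0.10 are assumed, to show a range.

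| Analysis of the primary outcome | ICC 0.02 | ICC 0.05–0.10 |
|---|---|---|
| Chi-square or logistic regression, unadjusted | 12.0–13.2% | 22–35% |
| Mantel-Haenszel by district, unadjusted | 12.3–12.8% | 22–34% |
| Mantel-Haenszel by district, estimated-ICC adjustment, chi-square reference | 6.1–6.4% | 6.9–7.1% |
| The same statistic on t with 12 df | 3.7–4.1% | 4.5–4.9% |
| Robust variance, normal reference | 9.2–9.5% | 9.1–9.3% |
| Robust variance × 7/6, t with 12 df | 4.7–5.0% | 4.6–5.0% |
| Centre-level t-test, 12 df | 4.7–5.0% | 4.6–5.0% |

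Regressing centre proportions on arm and district (t, 11 df) gave 5.0% at ICC 0.02. Monte Carlo error is about 0.15 to 0.25 percentage points.

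Dividing the district Mantel-Haenszel statistic by the true design effect gave 4.6–5.2%. The excess in the adjusted version therefore comes from estimating the ICC from 14 centres and then treating it as known.

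**Mantel-Haenszel stratified by centre.** Every centre holds one arm. Within a centre, observed equals expected and the variance is zero, so the statistic is 0/0.

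**Power with a small-sample reference.** The same standardised difference of 3.248, on a noncentral t, gives 84.6% with 12 df (critical value 2.179) and 84.0% with 11 df (critical value 2.201).

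**The case against.** The strongest reply is that the article does commit to adjusting every outcome for clustering, and the primary outcome is one of them. On that reading the 12% figure describes analyses the authors do not intend. The plan may be a cluster-adjusted logistic regression, close to what is recommended here, with details in the full protocol (version 1.2, not shown) or a statistical analysis plan. This largely stands. The 12% is conditional on unadjusted use, and the random-effect structure or degrees of freedom need not appear in an article. What remains is that the article itself lists competing methods without rank, and that two ordinary ways of honouring its adjustment sentence still exceed 5% with 14 centres.

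Other parts of the objection also stand:

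- A reader might infer that the Mantel-Haenszel analysis is undefined. That holds only if centre is the stratum. The article names no stratum, and the only randomisation stratum is district.
- A reader might infer that assigning Mantel-Haenszel statistics to all outcomes is impossible for survival or score data. It is not: the log-rank test is of that type, and mean-score extensions exist.
- The chi-square sentence covers categorical data in general. Only the logistic regression sentence mentions the primary outcome specifically, so chi-square as a rival primary test is an inference.
- Leaving district out of the model is not shown to inflate error: centre-level analyses gave about 5% with and without it.
- For PSQ-18 and KAP, ignoring positive within-person correlation often makes the standard error of a time-by-arm contrast too large. No inflation of error is claimed there.

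**Conclusion.** The point holds in a limited form. The article does not fix which analysis of the primary outcome decides, or how clustering is handled with 7 centres per arm, so control at 5% is not assured. At the stated ICC of 0.02 the error is about 12.5% if chi-square, logistic regression or district Mantel-Haenszel is used unadjusted. It is about 9% with an uncorrected robust variance, and about 6% with district Mantel-Haenszel, an estimated ICC and a chi-square reference (7% at an assumed ICC of 0.05–0.10). With a t reference it is 5% or slightly less.

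A reader might conclude that the trial's error rate is more than double what it claims. The text does not support that: it promises an adjustment, and some ways of carrying it out hold 5%.

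The figures assume beta-binomial variation between centres, equal centre sizes within each arm, full recruitment to 448 evaluable patients, and no district effect.

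**What to change.** Name one primary analysis, on the intention-to-treat set, that handles clustering with a small-sample reference. Either of these would serve:

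- centre proportions regressed on arm and district, with t on 14 − 3 = 11 df; or
- a logistic mixed model with a random intercept for centre, a fixed effect for district and small-sample degrees of freedom.

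State that the unadjusted chi-square, t and Mann-Whitney tests are not used for between-arm inference. If a Mantel-Haenszel statistic is kept as a secondary analysis, give its strata, the clustering adjustment and the reference distribution. For the repeated PSQ-18 and KAP scores, replace ordinary linear regression with a linear mixed model with person and centre effects.

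This changes analysis wording only, needs no new data, and can be done in R, which the article already names. It should be settled before anyone sees outcomes by arm. The cost is wider intervals and lower, but correct, power: about 85% on t with 12 df (84% with 11 df), against the 90% stated.

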**Methods:**

This study will be a prospective cluster randomized controlled trial, conducted among 14 community health centers in Shanghai which were randomized as the intervention group and control group in a ratio of 1:1. The intervention group will use the CDSS in the consultation of patients with AF and the control group will maintain their usual care. The trial will include 498 patients with AF and the follow-up period will be 12 months. The primary outcome is set as the proportion of antithrombotic treatment prescriptions in agreement with recommendations in the latest China’s AF-related guidelines. The secondary outcomes are the frequency of consultation, the compliance rate of international normalized ratio (INR) in patients with warfarin, stroke morbidity, treatment compliance, medication satisfaction, and the cost-benefit analysis. Per-protocol (PP) analysis and the intention-to-treat (ITT) analysis will be conducted.

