### Settings and participants

The requirements for using the CDSS in community health centers are that their servers of the hospital information systems (HISs) are at least with eight-core central processing unit, 32 GB RAM, hard drive of 500 G, and operating system of Centos 7.2. Fourteen community health centers willing to participant in this study in Baoshan District and Jing’an District of Shanghai were recruited by researchers. Baoshan District and Jing’an District are in the suburb and urban area of Shanghai, respectively, so are geographically representative (Additional file 2).

The participants are GPs and patients with AF in the selected community health centers. For GPs, the inclusion criteria are that they work in GP consulting rooms or the AF special consulting rooms in their community health center, are willing to participate in the study, and can complete the pre-training on AF management and CDSS use. They will be excluded if they rarely use computers in their daily work, or cannot complete the whole study.

Patients will be included if they are 18 years old or older, diagnosed with any type of AF or atrial flutter (ICD-10 codes shown in Additional file 3) during a consultation or in medical history, registered with GP for at least 1 year, and are willing to participate in the study and sign the informed consent (Additional file 4). They will be excluded if they are diagnosed with end-stage disease such as advanced tumors, or their expected survival time is less than 1 year, or are unable to cooperate with the study due to illiteracy or dementia, or cannot continually consult in the registered community health centers in the next 1 year due to objective conditions such as moving, or with valvular AF or prosthetic valves, or are participating in other clinical trials related to AF, or are pregnant or breastfeeding. Subjects can reserve the right to drop out due to any reason or without reason and at any time during the study. If any incident happens to the subjects, such as death, disability, or dementia, they could withdraw from the study after applying by their legal representatives and evaluating by researchers. Subjects who are pregnant during the follow-up and plan to give birth will be considered as withdrawal.

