#### Preparation

Prior to be used, the CDSS will be embedded into the HIS of community health centers in the intervention group. The GPs will be trained in the use of the CDSS within the intervention group by developers from Ping An Healthcare and Technology Co.Ltd., and GPs of both groups will be trained in AF management by the researchers. After training, the training materials will be bound into a handbook and provided to the GPs for free.

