##### Initial patients

Initial patients is defined as the patients who see the doctor in community health centers for the first time due to AF and have not been treated with any anticoagulants. The management interface is shown in Fig. 1a. The management procedures are in order:
Electrocardiogram (ECG) and echocardiography as in Fig. 1b. GPs will need to choose the appropriate option according to the patient’s ECG and echocardiography. If the ventricular rate is faster than 100 beats per minute or slower than 60 beats per minute, or if echocardiography is unavailable, or if a valvular disorder is suggested, the CDSS will advise referring the patients to superior hospitals to first regulate the ventricular rate, check the echocardiography, or treat the valvular disorders.Those patients with ventricular rates ranging from 60 to 100 beats per minute and echocardiography reported as normal valvular function can continue with the CDSS. The anticoagulants, including warfarin and NOACs, and medical history including initial AF, Grave’s disease, cancer, recent stroke, and cardiovascular heart disease (CHD) are shown in Fig. 1b. If patients are taking such drugs, the CDSS will change to the follow-up interface. If the patients are diagnosed with any one of the diseases, the CDSS will advise referral.Laboratory findings are shown in Fig. 1b. The CDSS will autoload relevant and latest laboratory findings within the last 3 months recorded in HIS. The required parameters are systolic and diastolic pressure in mmHg, hemoglobin (HGB) in g/L, hematocrit (HCT) as a percentage, platelet count (PLT) in units 10 [9]/L, alanine aminotransferase (ALT) and aspartate aminotransferase (AST) both in U/L, total bilirubin (TBIL) in μmol/L, direct bilirubin (DBIL) in μmol/L, blood urea nitrogen (BUN) in mmol/L, serum creatinine (Scr) in μmol/L, glomerular filtration rate (eGFR) as ml/min/1.73 m^2^), activated partial thromboplastin time (APTT) and prothrombin time (PT) both per second, left atrial diameter (LAD), left ventricular end-diastolic (LVIDd) and left ventricular end-systolic (LVIDs) all in mm, left ventricular ejection fraction (LVEF) as %, free T3 (FT3) and free T4 (FT4), both as pmol/L, thyroid-stimulating hormone (TSH) in IU/ml, serum potassium (K) as mol/L and NT-proBNP in pg/ml. Missing information in HIS will be corrected by GPs asking the patients.Medical history and drugs are shown in Fig. 1b. Detailed medical history included the presence or otherwise of vascular disease, cirrhosis, dialysis-dependent renal disease or renal transplantation, hypertension, heart failure, diabetes, a major ischemic stroke within 2 weeks, bleeding, other hemorrhagic diseases, peptic ulcer, perioperative period, labile INR, excessive alcohol drinking, pregnancy, and undesired long-term anticoagulation. Current drugs include vitamin K antagonist (VKA), antiplatelet, and non-steroidal anti-inflammatory agents (NSAIDs).CGA as seen in Fig. 1a, where if necessary, GPs can choose one or more assessments for patients, including fall risk and balance, cognition, and emotional and psychological disorders.Finally, recommendations will be provided by the CDSS, including scores, risk levels, and suggestions on treatment, referral, and follow-up, according to the risk of stroke and bleeding (Fig. 2). If the assessment result of a patient is the need for anticoagulation, the CDSS will also provide the linkages of usage and cautions, instructions, and tips on the interaction between anticoagulants and other drugs or food to GPs (Fig. 2) [29].

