### Outcomes

The primary outcome is the proportion of antithrombotic treatment prescriptions, in agreement with recommendations in the AF guidelines. It is defined as the agreement rate between the doctor’s anticoagulation prescriptions for newly diagnosed patients and the system’s recommendations, including prescribing anticoagulation drugs or recommending referral to superior hospitals for patients with anticoagulation indications, and refraining from anticoagulation for patients without such indications or with contraindications.

The safety outcomes, such as the incidence of bleeding events, all-cause mortality and in-patient events related to AF or AF complications will be reported. Referring to the Guideline of stroke prevention in Chinese patients with atrial fibrillation (2017), bleeding events are classified as minor and major bleeding [4].

The secondary outcomes contain seven items:

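### As worded, the only named subgroup factor exists in the intervention arm alone and cannot test effect modification; the time point of the 'anticoagulants used' stratum must also be fixed

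*Protocol article*

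**What the plan says.** Statistical analysis names one subgroup factor: "subgroup analyses will be conducted by whether the CDSS is installed and used in all general clinics or only the AF special consulting room". It then adds: "The sensitivity analyses will be performed by age strata, gender, resident district, and anticoagulants used". No time point is given for the last of these strata.

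Three other places bear on the subgroup factor:

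- Preparation says that "the CDSS will be embedded into the HIS of community health centers in the intervention group".
- The abstract's Methods paragraph says: "The intervention group will use the CDSS in the consultation of patients with AF and the control group will maintain their usual care".
- Settings and participants admits GPs if "they work in GP consulting rooms or the AF special consulting rooms in their community health center", without limiting this to one arm.

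Randomization and blinding names location as the only stratification factor.

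Two places bear on the drug stratum. Outcomes scores the anticoagulation decision for newly diagnosed patients. Agreement covers "including prescribing anticoagulation drugs or recommending referral to superior hospitals for patients with anticoagulation indications", and also "refraining from anticoagulation for patients without such indications or with contraindications". The section Initial patients describes people who "see the doctor in community health centers for the first time due to AF and have not been treated with any anticoagulants".

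**The concern.** A subgroup analysis in a randomised trial asks whether the treatment effect differs between levels of a factor. That requires the factor to be defined in both arms, preferably from information that precedes allocation. Here it is defined by where the tool is installed and used, and a control centre has no tool. The word 'used' also brings in behaviour after allocation. Centres that run the tool in every clinic may differ in size, staffing or AF caseload from those that confine it to one room, and such differences could pass for an effect of the roll-out model.

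The drug stratum raises a separate problem. If it records what was prescribed after allocation, then for the primary outcome it splits patients by most of what the outcome measures. A real effect would shrink within strata, and a reader could take that as evidence that the main result is fragile.

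**Working it through.** **1. Who can be classified.** There are 7 centres per arm (Sample size).

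| Arm | CDSS present | Value of the subgroup factor as worded |
|---|---|---|
| Intervention, 7 centres | yes | all general clinics, or AF special room only |
| Control, 7 centres | no | none |

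Two of the four arm-by-factor cells are empty, so an interaction cannot be estimated.

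**2. Pooled controls do not rescue it.** Let A and B be the results in the two sets of intervention centres, and C the result in all controls. The difference between the two subgroup effects is (A − C) − (B − C) = A − B. The controls cancel, and what remains is the non-randomised contrast among 7 centres.

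**3. Size of that contrast.** Sample size gives 12.64% v 28%, ICC 0.02, 90% power, two-sided 5%, and 448 patients (498 after 10% loss).

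The plan's figure is approximately reproduced. The two-proportion formula gives 143 per arm. The design effect is 1 + 29 × 0.02 = 1.58, and 143 × 1.58 = 226 per arm, or 452 in total. Also 448/0.9 = 498. The sample size is not at issue here.

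For the layout contrast, take the average of 448/14 = 32 patients per centre, with design effect 1 + 31 × 0.02 = 1.62. The effective size of a set of k centres is 32k/1.62. The split is not given, so it is assumed. Power = Φ[(0.1536 − 1.96 × SE0)/SE1], where SE0 uses the pooled proportion and SE1 the separate ones.

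Example, 3 v 4 with the lower rate in the smaller set: effective sizes 59.3 and 79.0, SE0 = 0.0705, SE1 = 0.0664, and (0.1536 − 0.1382)/0.0664 = 0.23, so power is 59%.

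| Split | Lower rate in smaller set | Higher rate in smaller set |
|---|---|---|
| 1 v 6 | 26% | 44% |
| 2 v 5 | 48% | 57% |
| 3 v 4 | 59% | 62% |

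These figures are optimistic, because the normal approximation ignores the small number of centres.

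**4. Drug stratum, if it means use after allocation.** For illustration, take 12.64% and 28% as agreement among patients with an indication, and let a share f of that agreement come through referral (f is not in the protocol). Users then agree in both arms. Non-users agree only through referral, at a rate of pf/[1 − p(1 − f)].

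| f | Users, control v intervention | Non-users, control v intervention |
|---|---|---|
| 0 | 100% v 100% | 0% v 0% |
| 0.2 | 100% v 100% | 2.8% v 7.2% |
| 0.4 | 100% v 100% | 5.5% v 13.5% |

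The 15.4-point difference becomes 0 in users and 0 to 8 points in non-users.

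The protocol does not restrict the stratum to indicated patients, so now include the rest. Assume that a share q = 80% to 90% is indicated, that e = 2% to 5% of the others receive an anticoagulant, and that f = 0 to 0.3. Let U = qp(1 − f) + (1 − q)e be the share of users. Agreement is qp(1 − f)/U in users and [qpf + (1 − q)(1 − e)]/(1 − U) in non-users.

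| | Control | Intervention | Difference within a scenario |
|---|---|---|---|
| Users | 88–98% | 94–99% | 1 to 6 points |
| Non-users | 11–25% | 13–31% | 2 to 7 points |

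The overall difference in these scenarios is q × 15.36, that is 12.3 to 13.8 points. The effect is strongly compressed but remains estimable.

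**The case against.** On the subgroup, one can say that clinic setting exists in both arms, that the wording is only loose, and that a comparison by roll-out model within the intervention arm is ordinary implementation reporting for which the protocol claims nothing confirmatory. The first point is true, but it shows that a usable factor is available, not that the plan uses it. The last point stands if the analysis is labelled descriptive; at present it is called a subgroup analysis.

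On the drug stratum the objection has more force. No time point is stated, and the strata are not tied to the primary outcome. Patients with AF already in their history may enrol, and the follow-up interface covers people already on warfarin or a NOAC. Use at enrolment, or drug type, are therefore possible readings. Use at enrolment would be a valid baseline stratum, though constant for untreated initial patients. Drug type recorded after allocation would place both strata in the users row above for the primary outcome.

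A reader might infer that this stratum simply is the outcome and that its odds ratio is undefined. The documents do not support that: referral and justified refraining also count as agreement, and the undefined odds ratio arises only in a subset of indicated patients that the plan does not specify. A reader might also infer that none of the sensitivity strata gives a randomised comparison. Age, gender and resident district are valid baseline factors. Calling those analyses sensitivity rather than subgroup analyses is a matter of label.

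**Conclusion.** The subgroup point holds on the text. The factor as worded has no value in control centres, so the analysis yields a contrast among 7 non-randomised centres, confounded by centre, and says nothing about effect modification. The power figures rest on an assumed split, 32 patients per centre and the protocol's ICC.

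The drug-stratum point is conditional. It holds for the primary outcome if use after allocation is meant, and it treats newly diagnosed patients as largely the untreated initial patients. The amount of shrinkage depends on the assumed values of q, e and f. For stroke, bleeding and other outcomes, post-allocation use is not the outcome but may lie on the path to it, so that comparison would also lack the protection of randomisation.

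The primary intention-to-treat comparison is untouched. The matter should be settled before analysis, but it does not threaten the main result.

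**What to change.** 1. Classify all 14 centres from information that predates allocation by how AF care is organised (AF special consulting room or general clinics). Test the arm-by-setting interaction allowing for clustering, and label it exploratory. Alternatively, keep the installation-layout contrast and call it descriptive within the intervention arm.
2. State when anticoagulants used is recorded. Restrict the stratum to status at enrolment, or drop it for the primary outcome.

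The cost is wording and one descriptor per centre, with no extra patients or visits. The drawback is low power for the interaction. With four equal cells its standard error is about twice that of the main effect, so the planned signal of 1.96 + 1.28 = 3.24 standard errors falls to 1.62. Power is then Φ(1.62 − 1.96), or about 37%, for an interaction as large as the whole planned effect. That is close to a best case, since 14 centres cannot fill four cells equally and layout is not a randomisation stratum.
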